### Comparison of Awaji classification to Awaji+IMC classification

To determine whether incorporating an IMC metric would improve diagnostic certainty of ALS, in Aim 2 we will prospectively compare the performance of two diagnostic schemes applied at initial presentation (Fig 2). Classification according to the Awaji Criteria will serve as the baseline diagnosis. The second diagnostic scheme will consist of the Awaji Criteria plus IMC, in which an abnormal IMC value will be considered the equivalent of an upper motor neuron sign in that limb. At six-month intervals each case will be assessed to determine if a definitive diagnosis has been made, and at what delay after symptom onset the diagnosis was made. The null hypothesis is that there is no difference in delay to an ALS diagnosis by incorporating IMC measurements into the Awaji Criteria.

**Fig 2 pone.0303053.g002:**
[figure not shown]
Experimental flow of Aim 2. Two provisional diagnoses will be made at initial presentation: one based on the Awaji criteria alone, and one based on the Awaji criteria with IMC assessment. Every 6 months a patient’s clinical record will be reviewed to assign a final diagnosis. After a final diagnosis is determined, the performance at initial presentation of the Awaji+IMC criteria will be compared to that of Awaji alone.

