## Introduction

Amyotrophic lateral sclerosis (ALS) is a progressive, uniformly fatal neurodegenerative disorder characterized by the loss of motor neurons in the brain and spinal cord. The loss of motor neurons results in paralysis and death, typically within 5 years and with 60% mortality by 3 years [1, 2]. ALS is characterized by significant phenotypic, genetic, and pathogenic heterogeneity. Phenotypic variability arises in the extent and location of upper motor neuron (UMN) or lower motor neuron (LMN) involvement, with typical ALS patients having a combination of both UMN and LMN symptomatology [1, 3].

On average, there is a delay of 12–16 months from the onset of symptoms to the diagnosis of ALS [4–6]. Currently, diagnosis of ALS is based on a history of progressive weakness, exam findings of LMN and UMN dysfunction, and exclusion of diseases that mimic ALS [7, 8]. One common reason for diagnostic uncertainty and delay in diagnosis is the lack of UMN features on physical exam, as UMN signs are not always present in early ALS [9, 10]. Needle EMG features of acute and chronic denervation were set equivalent to physical exam findings of LMN dysfunction in Awaji criteria to improve the diagnostic sensitivity [8]. While needle EMG is a reliable and widely available tool to confirm LMN degeneration, physical exam is the only practical way to assess UMN loss at the present time. An objective, widely available, electrophysiological assessment of UMN dysfunction is missing from current ALS diagnostic criteria.

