### Assessment of final diagnosis

A diagnosis of ALS or non-ALS condition will be made by the treating team and reviewed by a standing committee of neuromuscular specialists. Disagreement in diagnosis will be resolved by consensus; if a consensus cannot be reached the subject will be excluded from analysis. The clinical review committee will be blind to the IMC results and provisional diagnoses.

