**Fig 3 pone.0303053.g003:**
[figure not shown]
Cross-classification of initial Awaji with Awaji+IMC results by final diagnosis. A = Awaji criteria at initial visit, A+I = Awaji+IMC criteria at initial visit, +: definite or probable category, -: possible or uncategorized.

To determine whether adding IMC results in an earlier diagnosis of ALS, the time to diagnosis will be determined by when a patient achieves a diagnosis of ALS (as per *Assessment of final diagnosis*). At the end of the study, the time from first noticed symptom to diagnosis will be compared between Awaji and Awaji+IMC criteria using a one-tailed paired T-test.

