### Study organization

This is a multi-center study carried out in the ALS clinics at the University of Chicago (UC, primary site), Washington University, Massachusetts General Hospital, University of California at Irvine, and University of Miami. The protocol was approved by the Institutional Review Board at the University of Chicago (The University of Chicago Biological Sciences Division/University of Chicago Medical Center, FWA00005565) with local review at the participating institutions (University of California, Irvine, University of Miami, Washington University, Massachusetts General Hospital). The recruitment period is between 3/31/2021 and 12/31/2025. Both aims have the same recruitment period. All raw data will be transferred to and analyzed at the primary site (UC) to assure consistency in analysis and application of diagnostic criteria. Data from evaluations of individual patients will be uploaded by participating sites to a secure cloud-based data repository (RedCap and OwnCloud), including de-identified patient characteristics, exam and EMG reports, and raw sEMG data. A physician at the testing center will make a provisional classification according to the Awaji Criteria at the time of initial testing, IMC calculations will be performed by a technician who is blinded to the provisional classification, and provisional classification according to the Awaji+IMC criteria will be made after IMC calculation. Determination of a final diagnosis will be made as per *Assessment of final diagnosis* (Fig 2). Statistical analyses will be performed by a biostatistician who is not involved in determining the clinical diagnoses or the IMC calculation. Follow up clinical data will be abstracted by a research assistant from the electronic health records into a RedCap database.

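### The paired t-test on time to diagnosis can use only ALS cases diagnosed by study end, and with no common follow-up horizon it favours fast diagnoses; a premature non-ALS label may also go unchecked

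*Protocol article*

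**What the plan says.** All places are in the protocol article.

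- **Reviews.** The section comparing the Awaji and Awaji+IMC classifications says "At six-month intervals each case will be assessed to determine if a definitive diagnosis has been made". The Fig 2 legend says "Every 6 months a patient’s clinical record will be reviewed to assign a final diagnosis" and continues: "After a final diagnosis is determined, the performance at initial presentation of the Awaji+IMC criteria will be compared to that of Awaji alone".
- **Reference standard.** The section Assessment of final diagnosis sets it out as follows: "A diagnosis of ALS or non-ALS condition will be made by the treating team and reviewed by a standing committee of neuromuscular specialists". The committee is blind to IMC and to the provisional diagnoses. Disagreement goes to consensus, and "if a consensus cannot be reached the subject will be excluded from analysis".
- **Time analysis.** In the Statistical analysis section, "the time to diagnosis will be determined by when a patient achieves a diagnosis of ALS". Times from first symptom are then compared between the two sets of criteria at the end of the study, by a one-tailed paired t-test.
- **Calendar.** Under Study organization, "The recruitment period is between 3/31/2021 and 12/31/2025". No end-of-study date is given.
- **Natural history.** The Introduction says that on average "there is a delay of 12–16 months from the onset of symptoms to the diagnosis of ALS". Apart from patients with a known mimic, Aim 2 enrols people rated possible or uncategorized, so any ALS diagnosis comes after entry.

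**The concern.** A paired t-test has no place for a censored time. A patient with ALS whose diagnosis has not been reached at closure has no value to enter. Such patients are not a random subset: at any closure date they are those with the longest delay, and mostly those enrolled last. The comparison is meant to show whether IMC shortens the path to diagnosis, yet it would be made in patients whose path was short enough to finish. Because the test is named, this follows from a stated choice and not from a detail left to another document.

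A second, weaker issue concerns the 2x2 tables. The same six-monthly procedure settles ALS and non-ALS, and the article describes no later check of a non-ALS diagnosis. If one is given too early to a patient whom IMC had upgraded, the patient enters cell g (false positive) instead of cell c (true gain). Cell g lowers specificity and also enters the accuracy difference (c − g)/n, so one such case moves that numerator by two.

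**Working it through.** **1. The plan's own figures.** 243/0.6 = 405, and 410 are enrolled. At 60% this gives 410 × 0.6 = 246 expected ALS cases and 410 × 0.4 = 164 non-ALS (the plan says about 160). The 243 also reproduces for 9% against 4% at α = 0.05 and 90% power: a two-sided one-sample proportion test gives 246 with continuity correction and 247 by the arcsine method, and power at 243 is 91.6% by the two-sided normal formula. The detectable time reduction is (1.96 + 1.28) × 1.4/√243 = 0.29 months, matching the stated 0.3. None of these figures is in dispute.

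**2. Share of ALS cases undiagnosed at closure.** Inputs: accrual length T = 57 months (31 March 2021 to 31 December 2025, from the article). Assumed: uniform accrual, exponential delay from enrolment to ALS diagnosis with mean m, and data closure F months after recruitment ends. Then

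undiagnosed share U = (m/T) × (e^(−F/m) − e^(−(T+F)/m)).

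| Mean delay m (months) | F = 0 | F = 12 | F = 24 |
|---|---|---|---|
| 6 | 10.5% | 1.4% | 0.2% |
| 10 | 17.5% | 5.3% | 1.6% |
| 14 | 24.1% | 10.2% | 4.3% |

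For example, at m = 6 and F = 0: (6/57) × (1 − e^(−9.5)) = 0.105. At F = 0 the shares correspond to about 26, 43 and 59 of 246 ALS cases.

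**3. Mean delay among those diagnosed.** With the same inputs,

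mean = {m − (m/T) × [(F + 2m)e^(−F/m) − (T + F + 2m)e^(−(T+F)/m)]} / (1 − U).

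At F = 0 this gives 5.3, 7.9 and 9.9 months in place of 6, 10 and 14. At F = 12 it gives 5.7, 8.8 and 11.1.

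**4. From delay to time saved.** The article does not define the Awaji+IMC time in detail. Suppose that a patient upgraded by IMC is credited with the whole wait from initial visit to diagnosis, others with none, and that upgrading is unrelated to the wait. The mean saving then shrinks in the same ratio as the mean delay: 5.3/6 = 0.88 to 9.9/14 = 0.71 at F = 0, and 5.7/6 = 0.95 to 11.1/14 = 0.79 at F = 12. On this reading the saving is understated.

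**5. Premature non-ALS labels (illustration only).** Suppose that 10% of the 246 ALS cases (25) were labelled non-ALS, and that IMC had upgraded between 9% of them (the planned gain in sensitivity) and 60% (the preliminary arm sensitivity). With a true specificity change of −2%, the observed change is −(0.02 × 164 + q × 25)/(164 + 25). This is −2.9% at q = 0.09 and −9.7% at q = 0.60. Nothing in the article supports 10% as a rate; the step shows only how sensitive cell g is.

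**The case against.** A reader might infer that slow-declaring ALS is counted as a mimic by design. The documents do not support that. The review asks whether a definitive diagnosis has been made, which implies that a case without one stays open. A non-ALS outcome needs a treating-team diagnosis and review by a blinded committee, with exclusion if consensus fails. Some Aim 2 patients enter with a mimic already diagnosed and are not exposed to this error. Miscounting therefore needs a premature diagnosis that the committee accepts and nobody revisits. This part of the objection stands.

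It is also fair that an article may leave the follow-up length and closure date to the full protocol, so their absence is no error in itself. Closing on the last day of recruitment would leave the last patients with no six-monthly review, and nothing suggests that this is intended. The 10% to 24% range is thus a worst case.

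The delay inputs are uncertain too. The 12 to 16 months runs from symptom onset, while the model starts at enrolment, so a mean of 14 months is at the long end. If the 0 to 5 months of possible saving in Sample size justification is read as the wait from the initial visit, the mean is 2.5 months and the loss is about 2.5/57 = 4% even at F = 0.

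Finally, both errors would tend to make IMC look worse, so they are unlikely to create a false claim of benefit. What the objection does not remove is the named test: whatever the closure date, it excludes every ALS case without a diagnosis by then.

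**Conclusion.** The concern holds for the time comparison. A paired t-test at study end conditions on an ALS diagnosis by that date, and with 57 months of staggered entry and no common horizon this selects for fast diagnosis. Under the assumed accrual and delay (means of 6 to 14 months from enrolment), about 10% to 24% of ALS cases are lost if data close with recruitment and about 1% to 10% with a further 12 months. The size therefore depends on a closure date and a delay that the article does not state, and it is small if delays are short and follow-up runs a year or more past the last enrolment.

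The specificity issue holds only as a possibility: a premature non-ALS label may move a true detection from c to g, because no re-check is described. Nor should a reader infer that the sample size is wrong; the 243-case calculation is not affected.

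**What to change.** 1. Continue the six-monthly record reviews for every Aim 2 patient to one common time after the initial visit. The sponsor should choose the length.
2. At that horizon, or at the last available record if earlier, have the blinded committee re-review non-ALS labels in patients who had no established mimic at entry. Do this before the 2x2 tables are filled.
3. Replace the paired t-test on diagnosed cases with an analysis of time saved restricted to the horizon, using a method that allows censoring.
4. Report how many cases are still open at the horizon. As a sensitivity analysis, count them first as ALS censored at the horizon and then as non-ALS. This avoids having to define a group of suspected ALS.

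The cost is a readout that comes later, by up to the chosen horizon after the last enrolment, and some extra chart and committee review. Abstraction from the health record is already planned, so no added visits or tests are needed.

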### Assessment of final diagnosis

A diagnosis of ALS or non-ALS condition will be made by the treating team and reviewed by a standing committee of neuromuscular specialists. Disagreement in diagnosis will be resolved by consensus; if a consensus cannot be reached the subject will be excluded from analysis. The clinical review committee will be blind to the IMC results and provisional diagnoses.

### Statistical analysis

To determine whether adding IMC changes diagnostic accuracy, sensitivity, or specificity at initial assessment we will estimate and compare the sensitivity, specificity and overall accuracy of the Awaji+IMC criteria at initial evaluation relative to the Awaji criteria alone. If Awaji+IMC criteria detect more cases of ALS at initial evaluation, the distribution of diagnostic certainty will shift to higher certainty. A probable or definite category of Awaji criteria or a clinical diagnosis of ALS given by an ALS expert (as per *Assessment of final diagnosis*) will constitute a positive test result. The data will be summarized in two 2x2 tables as depicted in Fig 3. While there is not an independent “gold standard” for the diagnosis of ALS, very few patients (∼6%) in probable or definite ALS categories in the Awaji criteria turn out not to have ALS (denoted “e” in Fig 3) [25]. Given the role of Awaji Criteria measured in follow up appointments as a determinant of diagnosis, the specificity of the assessments at first visit will always be high. In addition, by construct if the Awaji criteria are positive then Awaji+IMC will be positive and thus the frequencies b and f in Fig 2 are structural zeros. In essence the question being addressed is the extent to which the sensitivity is increased by the incorporation of IMC relative to the decrease in specificity; these quantities will be estimated by $\Delta \hat{sens}=c/(a+c+d)$ and $\Delta \hat{spec}=-g/(e+g+h)$, respectively. The difference in accuracy will be estimated by *(c − g)/n*.

**Fig 3 pone.0303053.g003:**
[figure not shown]
Cross-classification of initial Awaji with Awaji+IMC results by final diagnosis. A = Awaji criteria at initial visit, A+I = Awaji+IMC criteria at initial visit, +: definite or probable category, -: possible or uncategorized.

To determine whether adding IMC results in an earlier diagnosis of ALS, the time to diagnosis will be determined by when a patient achieves a diagnosis of ALS (as per *Assessment of final diagnosis*). At the end of the study, the time from first noticed symptom to diagnosis will be compared between Awaji and Awaji+IMC criteria using a one-tailed paired T-test.

### Sample size justification

The sample size of the study was selected to determine whether IMC can materially reduce the number of false negatives (i.e., improve sensitivity) associated with the Awaji Criteria. The initial visit Awaji criteria have a sensitivity of 56–61% (probable or definite at initial visit with eventual diagnosis of ALS) [25, 26]. We will therefore target a true change in sensitivity (*Δsens*) of 9% and will test against the null hypothesis of *Δsens* of 4% (insufficient improvement). Power analysis suggests a total of 243 cases with a final diagnosis of ALS will be needed for an α < 0.05 and a power of > 90%. To estimate the number of patients that need to be screened we assume the distribution of patients enrolled is similar to that reported by Geevasinga et al [26] in which ∼60% of patients with “possible ALS” or “uncategorized” by the Awaji criteria at first visit were eventually diagnosed with ALS, and ∼40% were diagnosed with an ALS mimic. Therefore, the total sample size required is 243/0.6 = 405. We will enroll 410 patients, which will provide ∼160 patients for estimating the change in specificity.

To determine the magnitude of diagnostic time reduction that could be detected with this sample size, a power analysis was performed. We assume a possible reduction in time-to-diagnosis of 0 to 5 months, with a uniform distribution and standard deviation of 1.4 months. An N of 243 cases of ALS would provide 90% power, at α = 0.05, to detect a true reduction in time-to-diagnosis of 0.3 months.

### Study organization

This is a multi-center study carried out in the ALS clinics at the University of Chicago (UC, primary site), Washington University, Massachusetts General Hospital, University of California at Irvine, and University of Miami. The protocol was approved by the Institutional Review Board at the University of Chicago (The University of Chicago Biological Sciences Division/University of Chicago Medical Center, FWA00005565) with local review at the participating institutions (University of California, Irvine, University of Miami, Washington University, Massachusetts General Hospital). The recruitment period is between 3/31/2021 and 12/31/2025. Both aims have the same recruitment period. All raw data will be transferred to and analyzed at the primary site (UC) to assure consistency in analysis and application of diagnostic criteria. Data from evaluations of individual patients will be uploaded by participating sites to a secure cloud-based data repository (RedCap and OwnCloud), including de-identified patient characteristics, exam and EMG reports, and raw sEMG data. A physician at the testing center will make a provisional classification according to the Awaji Criteria at the time of initial testing, IMC calculations will be performed by a technician who is blinded to the provisional classification, and provisional classification according to the Awaji+IMC criteria will be made after IMC calculation. Determination of a final diagnosis will be made as per *Assessment of final diagnosis* (Fig 2). Statistical analyses will be performed by a biostatistician who is not involved in determining the clinical diagnoses or the IMC calculation. Follow up clinical data will be abstracted by a research assistant from the electronic health records into a RedCap database.

## Discussion

A paucity of disease-specific biomarkers to identify ALS patients early and objectively track disease progression has contributed to the slow development and testing of disease modifying compounds [27]. This is compounded by a need for high diagnostic certainty to enter ALS trials, as patients who are “uncategorized” by the Awaji criteria or are in the “possible” category are generally ineligible to participate in clinical trials. Earlier diagnosis should, therefore, be a priority for improving outcomes in ALS. One common reason for diagnostic uncertainty is the lack of UMN symptomatology on physical exam. There is accumulating evidence on the use of IMC as a biomarker for motor neuron diseases [11, 12, 28].

This study seeks to validate a simple technique for improving the diagnoses of ALS using IMC derived from surface recordings of muscle activity. The method is inexpensive, non-invasive, and could be implemented widely as it is performed using standard EMG equipment. Interpretation of IMC measurements would be performed with a standalone software package that analyzes surface EMG data and calculates IMC values, providing a binary qualitative interpretation of the results as normal or abnormal. IMC analysis can be done in patients who have significant muscle weakness as a Medical Research Council strength of ≥3/5 in the tested muscles will be adequate to perform the assessment.

A previous study by Jaiser et al suggested that IMC in the β frequency range in muscle pairs in the upper and lower limbs is not affected by age or sex [29]. As our study tasks are different from those employed in the aforementioned study, we will build a database of IMC across different ages, genders and ethnicities, to provide demographic-specific cutoff values for normal vs abnormal values of IMC. We will also investigate if IMC better differentiates ALS from LMN or UMN predominant mimics. If IMC is a good measure of UMN dysfunction, then it should not by itself distinguish ALS from UMN disorders like PLS or hereditary spastic paraplegia. Conversely, IMC should better differentiate between ALS and LMN-predominant mimics than the Awaji criteria alone.

## Conclusion

This study protocol is designed to test the validity of IMC as a diagnostic tool in ALS. If successfully validated, an abnormal IMC result could lead to earlier ALS diagnoses, increasing the number of patients with early ALS who will be eligible for available and oncoming treatments.
